#### Participant timeline {13}

Table 1 and Fig. 1 show the scheduling of evaluations and the participant timeline, respectively.

**Table 1 Tab1:** Schedule of assessments

	Pre-randomization	Post-randomization		
	Screening/baseline	Intervention (every session)	Post-treatment	6-month follow-up
SCV	X			
MINI	X		X	
BDI-II	X		X	X
DASS-21	X		X	X
CORE-OM	X		X	X
CORE-SFB		X		
SRS		X		
CRES-4				X
LSS	X			X
CCI			X	

*Abbreviations*: *SCV*, sociodemographic and clinical variables; *MINI*, International Neuropsychiatric Interview, *BDI-II*, Beck Depression Inventory second edition; *DASS-21*, Depression, Anxiety, and Stress Scale; *CORE-OM*, Clinical Outcomes in Routine Evaluation-Outcome Measure; *CORE-SFB*, Clinical Outcomes in Routine Evaluation-Short Form Version; *SRS*, Session Rating Scale; *CRES-4*, Consumer Reports Effectiveness Scale; *LSS*, Life Satisfaction Scale; *CCI*, Client Change Interview

**Fig. 1 Fig1:**
[figure not shown]
Participant timeline. MINI, International Neuropsychiatric Interview; BDI-II, Beck Depression Inventory second edition; DASS-21, Depression, Anxiety, and Stress Scale; CORE-OM, Clinical Outcomes in Routine Evaluation-Outcome Measure; CORE-SFB, Clinical Outcomes in Routine Evaluation-Short Form Version B; SRS, Session Rating Scale; LSS, Life Satisfaction Scale; CBT, cognitive behavioral therapy; PCT, personal construct therapy; PCT-RV, personal construct therapy virtual reality; CCI, Client Change Interview; CRES-4, Consumer Reports’ Effectiveness Scale

### Sample size {14}

The effect sizes reported in the literature about the differential efficacy of psychotherapy for depression are usually small [52]. Besides, the severity of the disorder of the targeted population is low (mild-to-moderate depression). Therefore, we anticipated a small effect size and selected 0.45 as the parameter for sample size calculation. The statistical power considered for the sample size calculation was 0.80, with a dropout rate of 5%, and an *α* significance level of 0.1 (one-sided). A total of 225 participants, 75 patients per arm, are required to detect a small effect size in our primary outcome measure (BDI-II).

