### Trial design {8}

This is a multi-center superiority randomized clinical trial, comparing the efficacy of two novel brief treatment modalities, PCT and PCT-VR, to CBT, a well-established treatment, with respect to their efficacy in treating young adults with mild-to-moderate depression. The comparison between PCT and PCT-VR will reveal the differential efficacy of including a VR app in the latter condition. The patient allocation ratio is 1:1:1.

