The PCT therapy protocol will be based on the case conceptualization as described by Winter and Procter [34] and on a series of texts describing the applied form of PCT [16, 25, 33] as well as on previous literature on PCT for adult depressive patients [35]. These include detailed objectives and tasks for each session that are summarized here.

In the first session, patients are welcomed, their complaints are clarified, and their constructions about themselves and the problems they face are explored (including attributions and possible solutions). In the second session, the RGT is administered, and in the third session, some of the results of the grid analysis are discussed with the patient in an effort to reach an enriched view of themselves and their problem(s). Any diagram used for this exploration of identity will be two-dimensional (2D). Sessions 4 to 9 will be focused on the different aspects of the construct system which need further exploration and reconstruction (cognitive conflicts, construction of “ideal self,” construct differentiation, constriction, family constructs, etc.). As needed, according to the details of each particular case, changes occurring in therapy will be related to the construction of self and others reflected in the results of the RGT. At the end of the ninth session, patients will be asked to rate again the grid elements with the same personal constructs elicited in session 2. In the tenth session, results of this end-of-therapy grid will be visualized and discussed, along with future prospects and elaboration of their personal projects.

The PCT-VR therapy protocol will be identical to the one just described with the exception of the sessions (mainly 3 and 10) in which the constructions of self and others derived from the grid analysis are visualized and explored with the VR application EYME, instead of 2D displays. The head-mounted display used is either Oculus Go or Oculus Quest.

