## Statistical methods

### Statistical methods for primary and secondary outcomes {20a}

Intention-to-treat analyses (i.e., using outcomes from all randomized participants) will be performed for the main outcomes. Linear mixed models will be used to analyze and to compare treatment effects for the three treatment conditions (CBT, PCT, and PCT-VR). Baseline measurements, gender (coded as woman/male/not-binary), age, and clinical variables will be entered in the model as covariates. Pairwise comparisons will be used to test the hypothesis that PCT will lead to better outcomes than CBT and that PCT-VR will result in better outcomes than PCT. For all the analyses, effect sizes will be calculated.

In addition to the statistical significance, the proportion of patients who attain clinically significant improvement on the outcome measures will be calculated and compared between treatment conditions. The clinically significant improvement will be determined considering the proposal of Jacobson and Truax. For them, two conditions must be met: reliable change (reliability of pre-to-post difference in scores not being produced by chance) and clinically significant change (post-treatment scores lying in the normal instead of the clinical range). To test the differences in frequencies between the treatment conditions, a chi-square test will be applied.

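### The stated sample-size inputs give 48 patients per arm, not 75; splitting alpha over three comparisons gives 75, but no split is stated and the analysis section names only two

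*Protocol article*

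**What the plan says.** All of the inputs are in the protocol article, section Sample size {14}:

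- Effect: "we anticipated a small effect size and selected 0.45 as the parameter for sample size calculation". The metric is not named.
- Power and dropout: "The statistical power considered for the sample size calculation was 0.80, with a dropout rate of 5" per cent.
- Alpha: "significance level of 0.1 (one-sided").
- Result: "A total of 225 participants, 75 patients per arm, are required to detect a small effect size in our primary outcome measure (BDI-II").

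The section names no test and no adjustment for multiple comparisons. Trial design {8} gives equal allocation: "The patient allocation ratio is 1:1:1".

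The contrasts are described elsewhere. The last paragraph of Background and rationale {6a} sets out three: PCT-VR against PCT and PCT-VR against CBT as the main hypothesis, and PCT against CBT as a secondary one. Statistical methods {20a} names two. It begins "Pairwise comparisons will be used to test the hypothesis that PCT will lead to better outcomes than CBT" and adds PCT-VR against PCT. PCT-VR against CBT is not listed, and no per-comparison level or adjustment is given.

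**The concern.** The section gives a full set of inputs and says that they require 225 patients. A reader who puts those inputs into the usual two-group formula gets 144. This is a printed calculation that does not reproduce, which is different from detail left to an analysis plan.

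At stake is the per-comparison error rate. If 75 came from splitting alpha over three comparisons, each test was planned at about 0.033. If the printed 0.1 applies to each test, it is three times as large, and the planned power is not 0.80. The analysis section does not settle the matter, because it is silent on adjustment and lists a different number of contrasts from the Introduction.

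**Working it through.** **Inputs.** d = 0.45, power 0.80 (z = 0.8416), one-sided alpha 0.1 (z = 1.2816), dropout 5%, three equal arms. Two assumptions are needed because the section is silent: 0.45 is a standardised mean difference, and the calculation is for a two-group comparison of means.

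**Formula.** n per arm = 2 (z_alpha + z_beta)^2 / d^2, with d^2 = 0.2025. Divide by 0.95 for dropout and round up.

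**Inputs as printed.**
2 × (1.2816 + 0.8416)^2 / 0.2025 = 2 × 4.508 / 0.2025 = 44.5, so 45 evaluable.
45 / 0.95 = 47.4, so 48 enrolled per arm and 3 × 48 = 144 in total. A noncentral-t calculation also gives 45 and 48.

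**The printed 75, reproduced.** With alpha 0.1 / 3 = 0.0333 one-sided (z = 1.8339):
2 × (1.8339 + 0.8416)^2 / 0.2025 = 2 × 7.158 / 0.2025 = 70.7, so 71 evaluable.
71 / 0.95 = 74.7, so 75 enrolled per arm and 225 in total.

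**Other variants tried**

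| Variant | Evaluable per arm | Enrolled per arm |
|---|---|---|
| One-sided 0.1, unadjusted | 45 | 48 |
| One-sided 0.1 split over two comparisons (same as two-sided 0.1) | 62 | 66 |
| One-sided 0.1 split over three, Bonferroni, normal approximation | 71 | 75 |
| As above, noncentral t | 72 | 76 |
| One-sided 0.1 over three, Sidak, normal approximation / noncentral t | 70 / 71 | 74 / 75 |
| Two-sided 0.05 | 78 | 83 |
| Three-group F test at 0.1, three ways of converting 0.45 to f | 52, 58, 77 | 55, 62, 82 |

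Of these, the variants that land on 75, or within one of it, all adjust for three comparisons. Adjusting for the two contrasts named in the analysis section gives 66 per arm (198), not 75.

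**What 75 per arm delivers.** 75 × 0.95 = 71.25, so 71 evaluable. Power is approximately Phi(d × sqrt(71/2) − z_alpha), with sqrt(35.5) = 5.958.

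| Effect (SD) | d × 5.958 | Power, one-sided 0.10 | Power, one-sided 0.0333 |
|---|---|---|---|
| 0.45 | 2.681 | 0.92 | 0.80 |
| 0.30 | 1.787 | 0.69 | 0.48 |
| 0.20 | 1.192 | 0.46 | 0.26 |

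The effect detectable with 80% power is (z_alpha + 0.8416) × sqrt(2/71): 0.36 SD at 0.10 and 0.45 SD at 0.0333. For comparison, 0.20 SD at one-sided 0.10 would need 2 × 4.508 / 0.04 = 225.4, so 226 evaluable per arm.

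**The case against.** The strongest reply is that the calculation may be sound with one step left unreported. The trial has three arms, the Introduction states three contrasts, and dividing the printed alpha by three returns exactly 75 and 225 with the printed effect, power and dropout. That stands as the likelier explanation. It remains an inference, since no section mentions an adjustment, and the analysis section's two contrasts do not fit it.

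It can also be said that 48 rests on an assumed metric and test. That is true. But the F-test conversions tried do not give 75 either, so the choice of test alone does not close the gap.

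A reader might infer three stronger things that the protocol does not support:

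- *That the basis for the sample size is wrong.* It is shown not to follow as written. A benign calculation that gives 225 exists.
- *That the claim to detect a small effect is false.* The protocol defines no size bands and prints 0.45 in the same paragraph, so the reader is told what was powered. The word is loose, because 0.45 is nearer the common benchmark of 0.5 for a medium effect than 0.2 for a small one, but this is a matter of labelling.
- *That 0.45 is too optimistic for PCT-VR against PCT*, because the two protocols are the same "with the exception of the sessions (mainly 3 and 10"). The word mainly does not limit the difference to two sessions, and the Introduction argues that VR acts through engagement. How large that effect could be is a judgement that this arithmetic cannot settle.

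**Conclusion.** The point holds as a failure of the printed inputs to give the printed number: 48 per arm (144) against 75 per arm (225), a difference of 27 per arm and 81 in total. It rests on reading 0.45 as a standardised mean difference in a single unadjusted two-group comparison. A three-way split of alpha would account for the whole difference, but it is not stated in the sample-size section, and the analysis section neither states it nor lists three contrasts.

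The trial is not shown to be underpowered for 0.45. Under either reading of the printed alpha, power at 71 evaluable per arm is at least 0.80. The practical consequence is uncertainty about the per-comparison error rate (0.10 or about 0.033) and the matching power (0.92 or 0.80). For effects of 0.2 to 0.3 SD, power is well below 0.80 on both readings, so a null result should not be taken to exclude a benefit of that size.

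**What to change.** Keep 225 and correct the stated basis in one of two ways.

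1. **If alpha was split over three comparisons:** say in Sample size {14} that 75 per arm gives 80% power for 0.45 SD in each pairwise comparison at one-sided 0.0333, allowing 5% dropout, and name the three contrasts. Change Statistical methods {20a} to test the same three contrasts at that level. Amending the sample-size section alone would create a new mismatch, because the analysis section lists only two contrasts and no adjustment.
2. **If no adjustment is meant:** say that 75 per arm (71 evaluable) gives about 92% power for 0.45 SD at one-sided 0.10 in each comparison, and drop the statement that the listed inputs require 225.

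In either case, name the metric, replace the reference to a small effect with an effect of 0.45 SD, and report the power for 0.2 to 0.3 SD: about 0.46 to 0.69 at one-sided 0.10, or 0.26 to 0.48 at 0.0333.

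The sample size does not change. Option 2 costs wording only. Option 1 also commits the analysis to a stricter level per comparison and to a third listed contrast.

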### Recruitment {15}

Participants will be recruited from several health services in Barcelona and surrounding areas which already have agreements with the *Universitat de Barcelona*. In addition, we will disseminate an open call through social networks.

## Assignment of interventions: allocation

### Sequence generation {16a}

Participants will be randomized to one of three arms in a 1:1:1 ratio, stratified by health center. Assignment will be conducted with computer-generated random block sizes of 3 or 6, masked from the study staff.

### Concealment mechanism {16b}

The allocation sequence will be concealed from the researcher enrolling and assessing participants in sequentially numbered, opaque, sealed, and stapled envelopes. The aluminum foil inside the envelope will be used to render the envelope impermeable to intense light. Corresponding envelopes will be opened only after the enrolled participants completed all baseline assessments and it is time to allocate the intervention.

### Implementation {16c}

Randomization will be performed by a staff member of the Department of Clinical Psychology and Psychobiology of the *Universitat de Barcelona* completely blind to the study and to treatment conditions and with no clinical involvement in the trial. The trial coordinator will save the sequentially numbered, opaque, sealed, and stapled envelopes. Allocation will be made after the research assistant obtains the patient’s consent during the baseline assessment.

## Assignment of interventions: blinding

### Who will be blinded {17a}

Researchers, patients, and therapists will not be blinded since this is impossible due to the major difference between the groups (use of virtual reality in PCT-VR). Moreover, therapists and (senior) researchers will need to follow a manual related to the corresponding arm of the study. However, blinding to study hypotheses will be fostered by explaining to all patients and therapists that the study objective is to assess the efficacy of psychotherapy for young adults, regardless of the type of treatment. On the other hand, researchers conducting outcome assessments will be blind to treatment allocation.

### Procedure for unblinding if needed {17b}

There is no prevision that unblinding will be needed

## Data collection and management

### Plans for assessment and collection of outcomes {18a}

All data from questionnaires will be gathered using an automatized system (e.g., Qualtrics™), even if participants are physically accompanied by their therapist or evaluators when completing the forms. To ensure data collection in every stage (baseline, therapy monitoring, and follow-ups), a number of quality control procedures will be used, such as providing participants with warnings whenever a question has been left blank to minimize the frequency of missing answers, notifying the research coordinator indicating that a participant is not eligible (e.g., the score in the BDI-II is above 28), and warning the research team if a patient is at risk (e.g., suicidal ideation) or a participant has not completed the questionnaire.

Screening interviews will be conducted in synchronous videoconference settings by psychology graduates specifically trained in the MINI by researchers of the team. Interviewers will enter data in the data system right after the interview whereas participants will be emailed individualized links to complete baseline questionnaires (BDI-II, CORE-OM, and DASS-21). All diagnoses will be supervised by the trial coordinator to ensure validity and homogeneity throughout the recruitment process. Then, to monitor the psychotherapy process, participants will also be emailed individualized links to complete the CORE-SFB just before each session, and the SRS 3.0 for the therapeutic alliance at the end. The post-treatment assessment consists of all the baseline measures, including the MINI interview which will be performed, whenever possible, by the same evaluators who carried out the baseline interview and again supervised by the trial coordinator. In addition to these instruments, the change interview will also be conducted by a researcher who did not have previous contact with the patient. With respect to follow-up measures, participants will be emailed (and reminded by telephone, if necessary) an individualized link to the questionnaires containing the same assessment protocol as in previous time points plus the CRES-4, for evaluating treatment satisfaction.

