**Methods:**

The efficacy of this innovative intervention (PCT-VR) will be compared to PCT and to CBT in a randomized clinical trial. The study includes an appraisal of therapists’ adherence and independent assessments to preserve internal validity. The Beck Depression Inventory-II is the primary outcome measure for calculating both statistical and clinical significance, but other outcomes will also be assessed (e.g., functioning, well-being, anxiety, stress) at pre- and post-therapy and at 6-month follow-up. The trial will be conducted in a naturalistic context, mostly at the usual health care center of each patient. A sample of 225 participants is targeted to reach enough statistical power to accomplish the goals of the study.

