### Oversight and monitoring

#### Composition of the coordinating center and trial steering committee {5d}

This is a multi-center study coordinated by the University of Barcelona in collaboration with the Open University of Catalonia. The main trial team is formed by two principal investigators (AM, GF) overseeing all aspects of the study, training of staff, and taking supervision of the clinical development of the interventions. They will meet weekly to monitor the progress with specific subgroups of the research team and with the trial coordinator. The latter, in coordination with the other members of the research team, will manage participant recruitment and treatment allocations, organize data entry, and monitor safeguarding data quality.

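### The post-treatment MINI that defines remission is supervised by the trial coordinator, who manages allocations and is nowhere said to be blind

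*Protocol article*

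**What the plan says.** On blinding, the section Who will be blinded {17a} first concedes that "Researchers, patients, and therapists will not be blinded since this is impossible" and then makes one exception: "researchers conducting outcome assessments will be blind to treatment allocation". The abstract (Methods) presents "independent assessments to preserve internal validity" as a strength of the design.

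On the trial coordinator, the article assigns these tasks:

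- **Envelope custody**, Implementation {16c}: "The trial coordinator will save the sequentially numbered, opaque, sealed, and stapled envelopes".
- **Allocation**, Composition of the coordinating center and trial steering committee {5d}: the coordinator, together with other team members, "will manage participant recruitment and treatment allocations".
- **Eligibility diagnoses**, Plans for assessment and collection of outcomes {18a}: "All diagnoses will be supervised by the trial coordinator to ensure validity and homogeneity throughout the recruitment process".
- **Post-treatment diagnoses**, same section: the MINI will be "performed, whenever possible, by the same evaluators who carried out the baseline interview and again supervised by the trial coordinator".
- **Assessment in general**, Data management {19}: the coordinator is named as supervisor of the outcome assessors.

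On use of the MINI, the Secondary outcomes section has it repeated after treatment and compares the share of remitted patients between arms. Remission rates also appear in the first of the Specific objectives.

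On questionnaires, {18a} says they are captured electronically, "even if participants are physically accompanied by their therapist or evaluators when completing the forms".

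**The concern.** The MINI diagnosis is the between-arm outcome that rests on an assessor's judgement, so it is where assessor blinding has work to do. The BDI-II, CORE-OM and DASS-21 are filled in by patients who know their treatment, and no assessor blinding can protect those.

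If the person who reviews post-treatment diagnoses knows the arm, blinding the interviewer protects only the first half of the process. Borderline cases are the ones most likely to be discussed with a supervisor, and they are also where knowledge of the arm could tip a remission call. The trial tests declared superiority hypotheses (PCT-VR over PCT and CBT, PCT over CBT), so any tipping could favour one arm systematically.

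A smaller, separate point is that the wording on questionnaires leaves it possible for an unblinded therapist to be present while a patient completes an outcome measure, or rates the alliance with that same therapist on the Session Rating Scale (SRS).

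**Working it through.** No figure in the plan is at issue, so the check sets the sections side by side.

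**Step 1. Does the coordinator know the arm?** Holding sealed, opaque envelopes does not reveal it. Managing treatment allocations ({5d}) very probably does, since it is hard to manage who receives which therapy without knowing which therapy it is. This is an inference, as the article does not say so outright. No section says the coordinator is blind, and {17a} places researchers in general on the unblinded side, except those who conduct outcome assessments.

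**Step 2. Can the coordinator affect a diagnosis?** For recruitment diagnoses, {18a} gives the purpose of supervision as validity and homogeneity. The word again carries the same supervision over to the post-treatment MINI. Supervision meant to make diagnoses valid and uniform has to be able to influence them, but the article does not say whether the supervisor can overrule an interviewer.

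**Step 3. Which outcomes are exposed?**

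| Outcome | Who rates it | Exposed to the supervision gap? |
|---|---|---|
| BDI-II (primary) | Patient | No |
| CORE-OM, DASS-21 | Patient | No |
| SRS (alliance) | Patient | No |
| MINI remission (secondary) | Interviewer, supervised by the coordinator | Yes |

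**Step 4. How large could it be?** The article gives no expected remission rate and no rate at which supervision changes a diagnosis, so the bias cannot be estimated. The unit of exposure is simple. With 75 patients per arm (Sample size {14}), one changed call moves that arm's remission percentage by 100/75 = 1.33 points. With the planned 5% dropout, 75 × 0.95 = 71.25, so about 71 are assessed and one call moves it by 100/71 = 1.41 points. These are scale figures, not estimates of bias.

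**Step 5. Is the separation achieved elsewhere in the plan?** Yes, twice. Randomisation is done by a department staff member with no clinical part in the trial ({16c}), and the change interview goes to a researcher who has not met the patient before ({18a}). The post-treatment MINI has no comparable arrangement for its supervisor.

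**Step 6. Therapist presence.** The clause in {18a} is conditional: it says the electronic system is used even when someone is with the patient. The same section has personal links emailed for the baseline, session and follow-up questionnaires, so being alone may be the usual case. No questionnaire and no time point is excluded from the clause.

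**The case against.** Read literally, {17a} covers those who conduct assessments. The coordinator supervises them and does not interview, so the sections do not flatly contradict each other. That stands, and the point is therefore a gap and not a breach of the stated rule. It also stands that the coordinator's knowledge of the arm is inferred, that remission is secondary, and that a condensed article may leave supervision procedures to the full protocol. The last argument carries less weight here, because the article does assign the roles and the assignment itself creates the overlap.

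A reader might infer three stronger things that the document does not support:

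- **That interviewers are unblinded.** Seeing the same patient at baseline and after treatment does not reveal the arm, and {17a} says assessors are blind.
- **That predictable allocation and control of eligibility open the door to selection bias.** Simulating sequences of 75 with blocks of 3 or 6 equally likely, and always guessing the least-used arm so far, gives about 58% correct against 33% by chance. That assumes someone who tracks every past allocation in a centre, and the article states neither the sequence length per centre nor the mix of block sizes. Block sizes are masked from staff ({16a}), and envelopes are opaque and opened only once all baseline assessments are complete ({16b}). Under the same assumptions, even a guesser who uses all past information can be certain of only about 9% of allocations. Eligibility also depends on a BDI-II score that the system flags automatically. These safeguards largely answer the worry.
- **That therapists are planned to sit in on questionnaires.** The clause only allows for it, and a difference in its effect between arms would be conjecture.

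**Conclusion.** The blinding claimed for outcome assessment is not secured at the supervision of the post-treatment MINI. This rests on two assumptions: that managing allocations means knowing them, and that supervising a diagnosis can influence it. Both are the natural reading of the text, though neither is stated.

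The consequence is confined to the remission comparison, a secondary outcome. Its direction and size cannot be derived from the document. The BDI-II analysis, the sample size and the main hypothesis tests are unaffected. Therapist presence is a minor loose end in the wording. The point merits a change because the change costs little and would make the article's statements on blind and independent assessment hold for remission, not because the design is wrong as written.

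**What to change.** Choose one of two routes.

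1. **Keep the coordinator blind.** Move envelope custody, opening and allocation handling to the department staff member who already performs the randomisation. This must include the second randomisation that {11b} provides for patients who decline VR. That staff member would then see arm labels, which is harmless given no clinical role, provided the person also takes no part in assessment. This route is harder to sustain, because {18b} also has trial coordinators ask patients why they withdraw, and such talks can reveal the arm.
2. **Change the supervisor.** Leave the coordinator's other tasks as they are, and have the post-treatment MINI supervised by an existing MINI-trained team member with no role in allocation or therapy supervision. Senior therapy supervisors are not suitable, since {17a} makes clear that they work to an arm-specific manual.

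Then reconcile {16c}, {17a}, {18a}, {19} and {5d} so that each says who is blind and who handles allocations.

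Add one sentence to {18a}: patients complete the post-treatment and follow-up questionnaires and the SRS without the therapist present.

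The cost is a reassignment among existing staff and a few sentences. The first route adds slightly more coordination at each randomisation; the second adds a handover of post-treatment interviews to another supervisor.
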